#### Subgroup analyses

2.12.2.

Exploratory subgroup analyses will assess whether the effectiveness of the incentive conditions varies across demographic and residential subgroups. Interaction terms between incentive type (financial, social, or none) and participant characteristics (residential status, gender, and age group) will be included in the logistic regression models. These analyses will evaluate whether certain incentives are more effective for particular subpopulations, such as specific residential groups or demographic categories, thereby identifying potential differences in responsiveness across participant types.

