### Sample size

2.4

The sample size for this study was fixed at 4,809 individuals, representing the total number of users in the King's Cross Equiem database who met the eligibility criteria. Power analysis was conducted to evaluate the study's ability to detect differences between the three incentive conditions under varying levels of willingness to participate in the control group. Because the total N was fixed by the sampling frame, results are presented as minimum detectable differences (MDEs) in percentage points for each assumed control rate (29). Power for differences in proportions was calculated using standard two-sample methods for binary outcomes (30).

Due to limited directly comparable external estimates of baseline participation without incentives in similar digital-based recruitment contexts, a plausible range of control proportions (1%–70%) was assumed and used as a sensitivity analysis. Because EMA recruitment can yield single-digit participation rates in some settings (23), MDEs for low baseline proportions (1%–10%) are included within this range as part of the same fixed-N sensitivity framework. Power calculations were then conducted for each assumed proportion, using a Bonferroni-adjusted significance level of 0.01667 (0.05/3) to maintain a family-wise error rate of 0.05 across the three planned pairwise comparisons among the three conditions (31). Table 2 summarizes the assumptions and the corresponding minimum detectable differences.

**Table 2 T2:** Results of power analysis for detecting differences in willingness to participate across incentive conditions.

N	Proportion willing in control	Percentage point difference
4,809	0.01	1.16
4,809	0.02	1.53
4,809	0.03	1.81
4,809	0.04	2.04
4,809	0.05	2.24
4,809	0.06	2.41
4,809	0.07	2.57
4,809	0.08	2.72
4,809	0.09	2.85
4,809	0.10	2.97
4,809	0.20	3.86
4,809	0.30	4.36
4,809	0.40	4.61
4,809	0.50	4.66
4,809	0.60	4.52
4,809	0.70	4.18

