#### Sequence generation

2.7.1

Participants were randomized into three incentive groups (financial incentive, non-financial incentive, or no incentive) using a stratified block randomization procedure. Stratification was based on participant type within the Equiem communication platform (residents, visitors, and commercial occupiers). Randomization lists were generated using the Sealed Envelope online randomization service, which employed randomly permuted block sizes of 3, 6, and 9 to ensure a balanced allocation across incentive groups within each stratum. Sealed Envelope is a web-based clinical trial randomization platform that generates allocation sequences based on user-specified parameters (e.g., allocation ratio, stratification variables, and randomly permuted block sizes) and allows the sequence to be exported for implementation (33). The platform provides documentation on permuted-block and stratified randomization procedures, supporting transparent reporting and reproducible sequence generation. The randomization lists were generated by the researcher prior to participant assignment and without access to any identifying information (e.g., names or email addresses) stored on the Equiem platform.

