#### Primary outcome variable

2.9.1

The primary outcome variable of this study is the willingness to participate in a future smartphone ecological momentary assessment (EMA) study. The variable is measured through a binary response included in the intervention email. Participants could select either “*Yes, I would like to register my interest!”* (coded as 1) or “*No, I am not interested!”* (coded as 0). Operationally, “Yes” would be defined as completing the core demographic/residential relationship items and submitting a valid email address to register interest; “No” would be defined as selecting the non-interest option. Moreover, participants who did not respond to the invitation (i.e., did not click either option) would be coded as 0 (not willing) in the primary intention-to-treat analysis.

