### Data collection

2.10.

Data for this study were collected through online questionnaires hosted on the Give My View (GMV) platform, which was the pre-existing data collection system available for the project and therefore informed the implementation approach. GMV is a public citizen digital engagement platform developed by LandTech to facilitate community participation and feedback. Accordingly, the capabilities and limitations of the GMV platform, together with the randomized design of the study, informed the development of two-stage questionnaire combinations.

The email invitation contained two response links (“Yes”/“No”), each directing recipients to a corresponding questionnaire. Those selecting “Yes” completed a brief sociodemographic questionnaire capturing demographic characteristics and indicators of study interest; those selecting “No” completed a brief questionnaire capturing reasons for non-participation and incentive preferences (see Supplementary File S1).

To ensure responses were correctly attributed to the participant's assigned incentive condition and user category, separate questionnaire instances were created for each combination of incentive condition (financial, social, no-incentive), response option (Yes/No), and user category (residents, visitors, commercial occupiers), yielding 18 instances in total. Each instance was linked via a condition-specific URL and labeled with a structured identifier to support tracking and analysis (e.g., RFNY=Resident–Financial Incentive–Yes; VNICN=Visitor–No Incentive–No).

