### Data management

2.11.

Several procedures were implemented to uphold data quality and ensure data security. The GMV survey design required responses for four core demographic items (gender, ethnic group, age range, and relationship to King's Cross), while follow-up preference items were optional. Additionally, the platform's device recognition feature guaranteed that once a participant submitted a response, they were unable to access the survey again, thereby preserving the uniqueness of each submission. As data were collected directly in a pre-coded digital format on the GMV platform, manual data entry was unnecessary, reducing the risk of transcription errors and enhancing the overall accuracy of the dataset.

The primary outcome—the participant's binary decision to participate (“Yes” or “No”)—was derived directly from the raw data exported from the GMV platform. Each survey response was coded post-collection: responses from participants who completed the “Yes” survey were assigned a value of 1 and those who completed the “No” survey were assigned a value of 0. This coding process ensured consistent and accurate representation of the primary outcome for analysis.

All data storage, handling, and sharing procedures will comply with institutional data security and ethical guidelines. Study data will be cleaned and anonymised prior to any sharing. Access to identifiable and cleaned study data will be restricted to authorised members of the research team and approved project partners in accordance with prior data-sharing agreements.

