### Analysis plan

2.12.

The trial will be reported in accordance with the CONSORT guidelines for reporting randomized trials. The detailed statistical analysis plan has been published elsewhere (34). All analyses will follow the intention-to-treat principle, including all randomized invitees, to ensure a comprehensive assessment of the intervention's effectiveness (35). The primary analysis will compare the effectiveness of the three intervention arms. Secondary analyses will explore subgroup differences in response to the incentives as well as examine barriers to participation and alternative preferences. Sensitivity analyses will be conducted to evaluate the robustness of the findings. The following sections outline these analyses in detail.

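### The age and gender interaction models cannot be fitted on all randomised invitees, because the article describes no source of age or gender for nonresponders

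*Protocol article*

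**What the plan says.** Protocol article, section 2.12.2 (Subgroup analyses): "Interaction terms between incentive type (financial, social, or none) and participant characteristics (residential status, gender, and age group) will be included". The models meant are the logistic ones for willingness. This serves objective 3 in the Introduction, which names residential status, age group and gender. Section 2.12.1 calls the subgroup work exploratory and tests interactions at a two-sided 0.05.

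The outcome and analysis set are fixed elsewhere. Section 2.9.1, for the primary intention-to-treat analysis: "participants who did not respond to the invitation (i.e., did not click either option) would be coded as 0 (not willing". Section 2.12: "All analyses will follow the intention-to-treat principle, including all randomized invitees".

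The sources of the covariates are as follows.
- Section 2.10: people who used the Yes link "completed a brief sociodemographic questionnaire capturing demographic characteristics and indicators of study interest".
- Section 2.10: people who used the No link "completed a brief questionnaire capturing reasons for non-participation and incentive preferences".
- Section 2.9.1: a Yes requires the core demographic items to be completed. A No requires only that the non-interest option be selected.
- Section 2.11: the survey design "required responses for four core demographic items (gender, ethnic group, age range", with relationship to King's Cross as the fourth item. It does not say whether both forms carried these items.
- Section 2.7.1: participant type is held on the communication platform and is the randomisation stratum, so it is known for everyone. No section describes age or gender as held there.

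**The concern.** A logistic interaction needs the moderator for the zeros as well as the ones. Here most zeros are expected to be people who never opened a form; section 2.12.3 itself expects uninterested people not to click the No link. As described, whether age and gender are observed depends on the outcome. The model then either has no variation in its outcome or is restricted to people who clicked, which is a response made after randomisation and possibly affected by the arm.

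At stake is the age and gender part of objective 3. The Discussion uses it to argue that the trial can show whether incentives draw in some groups more than others. A clicker-only model could report such a difference when the incentive works equally well in every group. The sensitivity analyses in section 2.12.3 address missing outcomes, not missing covariates.

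**Working it through.** The plan gives no figure on this point, so there is none to reproduce. The check is where the covariates come from, followed by arithmetic under assumed response rates.

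**Inputs.** From the article: N = 4,809 (section 2.4); three arms with balanced allocation in blocks of 3, 6 and 9 (section 2.7.1); nonresponders = 0 (section 2.9.1). Assumed, because the article gives no observed rates: Yes rate 5%, No-click rate 3%.

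**1. Yes form only (plain reading of sections 2.9.1 and 2.10).**
- Invitees with age and gender: 0.05 × 4,809 ≈ 240, all with outcome 1.
- Zeros: 4,809 − 240 = 4,569, of whom 100% lack age and gender.
- The outcome is constant where the covariates are known, so no coefficient can be estimated. This holds at any uptake, including the 70% at the top of the range in Table 2.

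**2. Both forms (section 2.11 leaves this open).**
- No-clickers: 0.03 × 4,809 ≈ 144.
- Invitees with age and gender: 0.08 × 4,809 ≈ 385.
- Zeros without them: (4,569 − 144) / 4,569 = 4,425 / 4,569 ≈ 97%.

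Range over other assumed rates:

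| Yes | No-click | With age and gender | Missing, of all invitees |
|---|---|---|---|
| 1% | 2% | 144 | 97% |
| 5% | 5% | 481 | 90% |
| 10% | 10% | 962 | 80% |
| 30% | 10% | 1,924 | 60% |

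**3. What a clicker-only model estimates.** Among clickers the odds of Yes in an arm are the Yes rate divided by the No-click rate. Hence

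OR(clickers) = RR × (control No-click rate / incentive No-click rate).

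Suppose the incentive has RR = 1.5 in both sexes, with the same control uptake, and No-clicks fall from 3% to 2% in the incentive arm among women only.
- Women: 1.5 × 3/2 = 2.25.
- Men: 1.5 × 3/3 = 1.5.
- Ratio of odds ratios: 2.25 / 1.5 = 1.5, with no true difference in incentive effect.

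A second assumed case has Yes at 5% (control) and 7% (financial) in both sexes, so the all-invitee OR is (0.07/0.93)/(0.05/0.95) = 1.43 in each. If No-clicks fall from 5% to 3% among men only, the clicker-only ORs are (0.07/0.03)/(0.05/0.05) = 2.33 in men and (0.07/0.05)/(0.05/0.05) = 1.40 in women. The ratio is 1.67.

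**4. What can be estimated without nonresponder covariates.** Allocation is random, so it is independent of age and gender. In subgroup g,

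P(arm a | Yes, g) ∝ P(Yes | a, g) × 1/3.

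The odds of arm a against control among registrants in g therefore equal RR for arm a in g. The coefficient of g in a model of arm is the log ratio of risk ratios, from which the allocation ratio cancels.

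**The case against.** The strongest reply is that much of this rests on what the article does not say. It never states that the platform lacks age or gender: the passages on randomisation mention the fields used for stratifying and assigning, and they are not an inventory. The questionnaire is in a supplementary file and the detailed analysis plan is published separately; neither is shown. That stands. A reader might infer that age and gender are unobtainable and the models can never be fitted, but the article supports only that no such source is described.

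A reader might also infer that the model is certainly degenerate. Section 2.11 does not limit the four required items to the Yes form, so that too is one reading only.

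The intention-to-treat sentence cannot be wholly literal, since sections 2.12.4.1 and 2.12.4.2 analyse decliners only. This is fair, but those outcomes exist only for decliners, whereas the interaction models concern the primary outcome, which is defined for every invitee.

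The No-click rates by sex are assumed, and nothing in the article suggests that such a pattern occurred. The examples show that a false interaction is possible, not that it is likely.

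An unseen plan could name a responder set or imputation. The first would depart from section 2.12; the second would have little to rest on, with age and gender missing for every nonresponder.

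**Conclusion.** The point holds for age and gender. With the sources the article describes, the planned interactions cannot be fitted on all 4,809 invitees. They are either not estimable (Yes form only) or a comparison among clickers that conditions on a post-randomisation response (both forms). The counts rest on assumed rates of 5% and 3%; that the covariates are absent for every nonresponder does not depend on those rates.

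Severity is moderate. A reader might take this to undermine the trial's main result or the whole of objective 3. It does neither: the primary comparison uses arm and participant type, both known for everyone, and the participant-type interaction can be fitted in full. Two exploratory moderators are affected.

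**What to change.** 1. State which forms carried the demographic items, and whether the platform holds age and gender recorded before randomisation for all invitees. If it does, name that source and how registrations are linked to it; the logistic interactions can then stay.
2. Keep the logistic interaction on all 4,809 for participant type, using the platform category that defined the strata.
3. Otherwise, replace the age and gender interactions with an exploratory case-only analysis: among Yes registrants, multinomial logistic regression of assigned arm on age group or gender, adjusted for stratum, reported as ratios of risk ratios with 95% intervals.
4. If a Yes-versus-No comparison among clickers is shown at all, label it descriptive and do not read it as effect modification.

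The cost is a change of wording in the protocol and analysis plan, with no new data. The effect is on the risk-ratio scale, and uptake percentages by age or gender are not available. Precision will be limited: with 240 registrants split evenly over three arms and two sexes (assumed), each cell has 40, so the standard error of the log ratio of risk ratios is about √(4/40) = 0.32 and the 95% interval spans a factor of exp(1.96 × 0.32) ≈ 1.9 either way. The small number of registrants drives this. Adding the zeros, about 4,569/6 ≈ 761 per cell, would leave the standard error at √(4/40 + 4/761) ≈ 0.32.

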#### Sensitivity analyses

2.12.3.

Given the study design, some individuals who are not interested in the well-being study are expected not to click the “*No, I am not interested”* hyperlink to complete the corresponding survey, potentially resulting in missing data. To address potential bias from this nonresponse, sensitivity analyses will be performed to assess the robustness of findings (9).

These analyses will evaluate the potential impact of missing data on the primary outcome: willingness to participate in a future study. Because nonresponse is likely to be missing not at random (MNAR)—that is, individuals who are uninterested may simply close the email rather than actively opt out—alternative assumptions will be explored to assess how different missing-data mechanisms influence overall results (see Additional Document 2). By comparing results under these alternative assumptions with those from the main analysis, the sensitivity analyses will clarify the extent to which missing data may affect the estimated effectiveness of the incentives.

#### Additional outcome analysis

2.12.4.

##### Analysis of barriers to participation

2.12.4.1.

The first additional outcome analysis will focus on participants who decline to participate in the EMA study (i.e., those who select “No”). Each potential barrier to participation will be represented as a binary variable indicating whether a given reason was endorsed. Descriptive statistics will summarize the frequency and percentage of each reported reason, stratified by incentive condition. Graphical summaries (e.g., bar charts) will be used to visualize the most frequently cited reasons and their distribution across incentive conditions.

To examine whether endorsement of specific barriers varies by incentive type, separate Firth logistic regression models will be fitted for each reason, with incentive condition (financial, social, or no incentive) as the main predictor. Firth logistic regression will be used to reduce sparse-data bias and to address potential separation. Odds ratios (ORs) and 95% confidence intervals (CIs) will be reported for each incentive condition relative to the no-incentive group, and False Discovery Rate (FDR) adjustment will be applied across the set of reason-specific models to account for multiple testing.

The total number of reasons endorsed by each respondent will be analyzed as a count outcome using Poisson regression. A model including incentive condition as the main predictor will be fitted to assess whether the number of reported barriers differs across the financial, social, and no-incentive conditions. Incidence rate ratios (IRRs) and 95% confidence intervals (CIs) will be reported.

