#### Secondary outcome variable

2.9.2

The study also assessed two secondary outcomes among participants who indicated that they were unwilling to participate in the EMA study. The first secondary outcome captured the reason for unwillingness to participate. Participants were asked to identify one or more factors influencing their decisions not to participate. These factors included (1 = “Inadequate compensation”), app notification frequency (2 = “Too many notifications”), study duration (3 = “long/excessive study duration”), limited time availability (4 = “daily time constraints”), app download (5 = “Reluctance to install new app”), privacy concerns (6 = “privacy and data security concerns”), lack of interest (7 = “Lack of interest in the study”), and [8 = Other reasons(please specify)]. Participants were asked to “select the main reason(s) for not participating in the future research study” from this list.

The second secondary outcome assessed alternative incentive preference. This outcome was obtained only for participants who selected “*Inadequate compensation”* as their main reason for non-participation. These participants were subsequently presented with a list of seven potential incentive alternatives they preferred to be offered for a similar study in the future. They were asked, “Would any of these increase your likelihood to participate? Check all that apply” The incentive options were: nothing (1 = “Nothing will increase my likelihood”), guaranteed cash payment (2 = “£50 guaranteed cash on study completion”), gift card (3 = “Gift card on study completion”), prize draw (4 = “4× £100 cash prize draw”), personalized feedback (5 = “Personalized well-being feedback”), special event invitation (6 = “Exclusive post-research social & feedback event”), charity donation (7 = “Donation to charity”), and other (8 = “Other—please specify”).

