### Research ethics approval

4.1

The study was approved by the University of Manchester Research Ethics Committee (Division: School Level Review) (Review reference: *2023-17042-30162*) on 30/06/2023. Given the nature of the project, the risk of participant distress was considered minimal, as participation required explicit opt-in consent and the study topic was not sensitive. Participants were reminded that they were free to stop the survey at any time and were not required to answer any questions they preferred to skip.

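### Poisson regression is planned for a count whose valid values run from 1 to 8, so default Poisson intervals for the IRR will probably be miscalibrated, most likely too wide

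*Protocol article*

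**What the plan says.** Section 2.12.4.1 (Analysis of barriers to participation) restricts the analysis to decliners: "The first additional outcome analysis will focus on participants who decline to participate in the EMA study". For the number of barriers it says "The total number of reasons endorsed by each respondent will be analyzed as a count outcome using Poisson regression", with incentive condition as the main predictor, and "Incidence rate ratios (IRRs) and 95% confidence intervals (CIs) will be reported". It names no type of standard error and no check of dispersion.

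Section 2.9.2 (Secondary outcome variable) defines the item behind the count: "Participants were asked to identify one or more factors influencing their decisions not to participate". The prompt asked people to "select the main reason(s) for not participating in the future research study", and the list ends with the eighth option, "8 = Other reasons(please specify".

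Two other passages bear on the lower limit. Section 2.11 (Data management) says "The GMV survey design required responses for four core demographic items (gender, ethnic group, age range, and relationship to King's Cross"; the reasons item is not in that list. Section 4.1 (Research ethics approval) says that participants "were not required to answer any questions they preferred to skip".

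**The concern.** A Poisson variable can be zero, has no upper limit, and has a variance equal to its mean. A completed reasons item can be neither zero nor above eight. When most respondents tick one or two boxes, the counts cluster just above the floor and vary less than a Poisson variable with the same mean. A default Poisson fit then takes its standard error from the mean and overstates it.

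At stake is part of objective 4, which compares reasons for declining between incentive conditions. With inflated standard errors, a real difference between arms in the number of barriers is more easily reported as no difference. With ticking patterns of the opposite kind, the intervals would be too short.

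**Working it through.** **Inputs from the article.** Count range 1 to 8 for a completed item (section 2.9.2); Poisson model, IRR and 95% CI (section 2.12.4.1). The article gives no expected mean, variance, dispersion or number of decliners, so it has no figure to reproduce. Every distribution below is an assumption.

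**Formula.** For a Poisson model with a categorical predictor and the same count distribution in each arm,

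model-based SE of log IRR ÷ true SE = √(mean ÷ variance).

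A value above 1 means intervals that are too wide; below 1, too narrow.

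**One example by hand.** Suppose 1, 2, 3 and 4 reasons are ticked by 60%, 25%, 10% and 5%.
- Mean = 0.60 + 0.50 + 0.30 + 0.20 = 1.60.
- Mean of squares = 0.60 + 1.00 + 0.90 + 0.80 = 3.30.
- Variance = 3.30 − 1.60² = 0.74, so variance/mean = 0.46.
- SE factor = √(1.60 ÷ 0.74) = 1.47.

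The implied two-sided error rate of a nominal 5% test is P(|Z| > 1.96 × 1.47) ≈ 0.4%. A simulation of 20,000 data sets with 50 decliners per arm (an assumed number) gave 0.3% with model-based SEs and about 5.6% with robust SEs.

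**Varying the mean, with independent ticking.** Two families limited to 1–8 were used: a zero-truncated Poisson cut at 8, and a zero-truncated Binomial(8, p).

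| Assumed mean | Variance/mean | SE factor |
|---|---|---|
| 1.2 | 0.17–0.18 | 2.4 |
| 1.5 | 0.34–0.37 | 1.6–1.7 |
| 2 | 0.49–0.59 | 1.3–1.4 |
| 3 | 0.56–0.79 | 1.1–1.3 |

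For instance, the truncated binomial with mean 1.5 has p = 0.120 and variance 0.512, so the factor is √(1.5 ÷ 0.512) = 1.71.

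**Coverage with no true effect.** At assumed means of 1.5, 2 and 3, with 30 or 100 decliners per arm and 2,000 runs each, model-based intervals covered 97–100% and robust intervals 93–95%.

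**Patterns that close or reverse the gap.**
- Positively correlated ticks (zero-truncated beta-binomial): at correlation 0.2, variance/mean is 0.88 at mean 2 (factor 1.07) and 1.02 at mean 2.5 (0.99). At correlation 0.3 and mean 3 it is 1.26 (0.89).
- A minority ticking many boxes: 1, 2, 3, 4, 5, 6 and 8 reasons at 50, 20, 10, 8, 5, 4 and 3%. Mean 2.25; mean of squares 8.09; variance 8.09 − 2.25² = 3.03; ratio 1.35; factor √(2.25 ÷ 3.03) = 0.86. Nominal 95% intervals would then cover about 91%.
- The range 1–8 alone allows a variance up to (mean − 1)(8 − mean). At mean 2 that is 1 × 6 = 6, a ratio of 3.0.

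**If blanks are counted as zero.** With independent ticks the count is Binomial(8, p) and variance/mean is 1 − mean/8: 0.81 at mean 1.5 and 0.75 at mean 2, giving factors of 1.11 and 1.15. The dispersion, and the mean itself, therefore depend on how skipped items are coded.

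**The case against.** The strongest reply has three parts.

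First, a reader might infer that a floor of 1 and a cap of 8 by themselves force the variance well below the mean, so that the intervals must be far too wide. That does not follow. The range permits a variance above the mean, and modest correlation between ticks or a few heavy tickers is enough to produce it. The article reports nothing that rules this out. Too-wide intervals are the likelier outcome because the prompt asks for main reasons, but that is a judgement.

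Second, a reader might infer that the plan commits to model-based standard errors. It does not say so. Poisson regression with sandwich standard errors is still Poisson regression, and the separate statistical analysis plan, which is not at hand, may specify them. This stands as a limit on the point. Still, model-based errors are the usual default when nothing is said. The article does add such detail elsewhere: Firth regression for the individual reasons in the same section, and robust or bootstrap errors for the risk differences in section 2.12.1.

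Third, the absence of zeros is not shown to be enforced, since the reasons item is not among the required ones and questions could be skipped. This is fair, and it is why the handling of blanks belongs in the fix.

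It is also true that error in the likelier direction is conservative and does not inflate false positives.

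**Conclusion.** The point holds in a limited form. A completed count lies between 1 and 8, so the Poisson variance assumption will generally not hold, and default intervals for the IRR should not be relied on for 95% coverage. With few ticks per person they are too wide, by roughly 60–70% at a mean of 1.5 and 30–40% at a mean of 2 under the assumed distributions. With correlated or heavy ticking the excess disappears or reverses.

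These sizes rest on assumed distributions and on the use of model-based standard errors. The documents do not support a stronger claim that real differences will be missed. The consequence is confined to the precision of one additional analysis among decliners: the IRR remains a consistent ratio of mean counts, and neither the primary outcome nor the models for individual reasons are affected.

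**What to change.** Unless the statistical analysis plan already says so, add to section 2.12.4.1 that the Poisson mean model and the IRR are kept, with 95% CIs and p-values from robust (sandwich) standard errors, using HC3 or a bootstrap if decliners are few. Quasi-Poisson standard errors for the same count are an acceptable alternative. Either choice corrects the intervals in both directions, so the dispersion need not be known in advance.

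State also that a skipped reasons item is set to missing, not to 0.

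Do not switch to modelling the count minus one, because that changes the estimand. With means of 1.60 and 2.02, the planned ratio is 2.02 ÷ 1.60 = 1.26, whereas on the shifted scale it is 1.02 ÷ 0.60 = 1.70.

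The cost is one option in the analysis code and a sentence or two in the plan. The downside is that robust standard errors are slightly liberal in very small samples: the simulations with 50 decliners per arm gave null rejection rates of 5.6% and 6.7% instead of 5%.
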